## Abstract

**Background:**

Major depressive disorder (MDD) is a common severe mental disorder with enormous socioeconomic costs for the patient and society alike. Current pharmacological and psychotherapeutic treatments are ineffective in a substantial fraction of patients and can be accompanied by unwanted side effects.

**Methods:**

Using a novel non-invasive brain stimulation method to specifically target and modulate dysfunctional brain oscillations with high spatial and temporal precision this study will investigate the efficacy of EEG-triggered transcranial magnetic stimulation (TMS) to alleviate depressive symptoms in 28 patients with MDD in a 1:1-randomized, double blind, standard treatment-controlled pilot trial. In the experimental condition, stimulation will be brain oscillation-synchronized based on the EEG-extracted endogenous theta oscillation over left dorsomedial prefrontal cortex (DMPFC). The control condition will consist of standard TMS therapy following an FDA-approved intermittent theta-burst stimulation (iTBS) protocol over left dorsolateral prefrontal cortex (DLPFC). The treatment will be performed over four consecutive weeks (20 sessions) and the primary outcome will be the change in the Montgomery-Åsberg Depression Rating Scale (MADRS) after the last versus before the first treatment session.

**Discussion:**

The aim of the study is to gain exploratory evidence for the feasibility and efficacy of EEG-synchronized TBS of left DMPFC compared to a standard FDA-approved treatment (iTBS of left DLPFC) in a double-blind randomized parallel-design pilot clinical trial. Positive results will pave the way for a larger RCT to prove the superiority of personalized, brain oscillation-synchronized non-invasive brain stimulation therapies as novel, effective and well-tolerated treatment in MDD.

**Trial registration:**

*Trial Registration*: NCT06345651, date of registration: 2024-01-08, https://clinicaltrials.gov/study/NCT06345651The trial is conducted in accord with protocol version number 2022-09, Version 3. Recruitment started in January 2024, and recruitment is ongoing. The recruitment phase is projected to conclude by December 2026.

**Supplementary Information:**

The online version contains supplementary material available at 10.1007/s00406-025-02176-9.

## Introduction

### Background and rationale

Major depressive disorder (MDD) is a prevalent and severe psychiatric illness with a lifetime prevalence of 8–16% [1]. Standard treatments for MDD include antidepressant pharmacotherapy and psychotherapy, which are effective for many patients. However, a substantial fraction of patients does not achieve adequate response with these first-line approaches [2–4]. Such treatment-resistant depression is common—on the order of 20–30% of patients—underscoring the need for alternative or adjunctive interventions. In recent years, several novel therapies have emerged (e.g. ketamine/esketamine and psilocybin) to address treatment-resistant depression [5, 6]. In parallel, non-pharmacological treatments, including neuromodulation techniques, have gained prominence as strategies to improve outcomes in difficult-to-treat depression [7]. Besides antidepressant medication, light therapy, sleep-deprivation, electroconvulsive therapy and movement therapy are possible non-pharmacological treatments with a level A or B recommendation. Level A refers to at least one high-quality meta-analysis with overall consistency of results,Level B refers to at least one high-quality systematic review with consistency of results according to the Association of the Scientific Medical Societies (AWMF following the Oxford Centre for Evidence Based Medicine (OCEBM. Among neuromodulation approaches, electroconvulsive therapy (ECT remains the most efficacious for severe or refractory cases [8] (Level A evidence), but its cognitive side effects and limited patient acceptability drive the search for other options. Repetitive transcranial magnetic stimulation (rTMS) of the prefrontal cortex has emerged as a less invasive alternative that can modulate brain activity [9]. The 2022 German National Care Guideline (Bundesärztekammer (BÄK), Kassenärztliche Bundesvereinigung (KBV), Arbeitsgemeinschaft der Wissenschaftlichen Medizinischen Fachgesellschaften (AWMF). Nationale Versorgungsleitlinie Unipolare Depression—Langfassung, Version 3.2. 2022. 10.6101/AZQ/000505) provides a level B recommendation for the use of rTMS in treatment-resistant depression. In fact, high-frequency rTMS of left dorsolateral prefrontal cortex (DLPFC) shows definite antidepressant effects at the group level (level A recommendation) but its clinical efficacy is limited due to high inter-individual variability with response rates around 30% in real-world settings [9–12]. More recent consensus reviews with large-scale real-world studies report response rates up to over 50–60% depending on patient characteristics and treatment parameters [13] Recognizing this heterogeneity, experts emphasize that rTMS protocols should be tailored whenever possible and it is strongly advised that the choice of stimulation site and type is made at a specialized center, which is a level A recommendation [11, 14]. This points out the lack of a consensus regarding the use of different TMS protocols at the individual level and underscores the importance of addressing the existing heterogeneity by the advancement of personalized TMS treatment paradigms. One such FDA-cleared innovation is intermittent theta-burst stimulation (iTBS), a patterned form of rTMS delivered in only ~ 3 min per session. A landmark non-inferiority trial demonstrated, that iTBS to left DLPFC achieves antidepressant outcomes equivalent to traditional 10 Hz rTMS (≈37-min sessions) [15]. Thus, iTBS offers a time-efficient alternative with similar clinical benefit. In practice, iTBS is increasingly adopted as a standard protocol for MDD, enabling higher patient throughput and the possibility of accelerated treatment courses (e.g., through multiple-session-daily designs) in recent trials and reviews [13, 16]. Despite these advances, the field continues to seek ways to improve remission rates by optimizing how and e.g. *when* brain stimulation is delivered for each patient [17, 18].

Critically, MDD is not merely a psychological or chemical imbalance, but is associated with altered brain network activity and dysfunctional neural oscillations [19, 20]. Electroencephalography (EEG) provides an excellent basis for the development of biomarkers due to its high temporal resolution [21], which makes it an ideal tool for detecting these subtle but significant changes in real-time. For example, increased theta-frequency oscillations in frontal and limbic circuits have been linked to depressive pathology [18]. In the international Study to Predict Optimized Treatment in Depression (iSPOT-D), a large international multi-center randomized prospective practical trial on predicting pharmacological treatment outcome, patients with MDD had elevated theta activity in both frontal cortex and anterior cingulate cortex, which was associated with non-response to pharmacological treatment, whereas low theta activity was associated with treatment response, suggesting that excess frontal theta is a marker of an active, treatment-resistant depression network [22]. In contrast, patients with MDD did not differ from controls on frontal alpha asymmetry in this study [23]. This and other studies support frontal midline theta activity as a potential biomarker of MDD severity and prognosis [24–26]. The presence of abnormal frontal alpha asymmetry is also discussed as a biomarker indicative for MDD [27]. Overall, EEG-based measures offer a window into the dysfunctional brain circuitry of MDD and are being actively explored as objective biomarkers to guide and evaluate treatments.

The here proposed trial links these findings to the core hypothesis: that targeting and modulating these pathological brain oscillations in real-time may represent a more effective and personalized treatment strategy. A promising strategy to personalize rTMS is to time stimulation pulses in accordance with the patient’s intrinsic EEG rhythms [28, 29]. The physiological rationale is that brain networks cycle through fluctuating excitability states, and stimulating at specific phases of an ongoing oscillation can maximize neural impact [17, 28]. In the motor cortex, brain oscillation-synchronized high-frequency bursts of TMS, i.e., TMS triggered to the trough of the instantaneous sensorimotor µ-oscillation as detected by real-time EEG analysis, has been shown to consistently increase motor cortical excitability, similar to long-term potentiation, while targeting the positive peak of the µ-oscillation or random phase stimulation did not show this effect [30]. These findings suggest that the full therapeutic potential of rTMS to modulate dysfunctional brain networks can be more effectively exploited by personalizing rTMS therapy to individual brain states, such as brain oscillations. Exploiting this newly developed EEG-TMS technique, we have conducted a single-session proof-of-principle study to investigate the feasibility, safety and immediate neurophysiological effects of EEG-triggered brain alpha-oscillation-synchronized TMS of left DLPFC in 17 patients with unipolar antidepressant-resistant MDD [31]. EEG-triggered brain oscillation-synchronized TMS of left DLPFC was feasible in the majority of patients (15/17, ~ 88% success rate in achieving real-time EEG triggering) and reduced resting-state alpha power in the left DLPFC (the stimulation site) compared to control conditions. Side effects reported were limited to mild discomfort at the site of stimulation. As this was a single-session proof-of-principle trial, no clinical outcome measures were obtained. These findings demonstrated that EEG-synchronized rTMS of left DLPFC can be applied safely and has the potential to interact with and modulate dysfunctional brain oscillations in patients with MDD.

Encouraged by these pilot results, research teams have begun evaluating EEG-synchronized rTMS in clinical trials. Notably, a recent double-blind randomized controlled trial examined alpha-phase-synchronized prefrontal rTMS in adults with treatment-resistant depression over a full 6-week, 30-session course [32]. In this trial 28 treated patients were randomized to receive left prefrontal rTMS either with the first pulse of each train locked to the individual’s preferred prefrontal alpha phase (“SYNC” group), or with that pulse delivered at arbitrary phases (“UNSYNC” control), with all other stimulation parameters held constant. Results showed that the SYNC condition was feasible over the prolonged treatment course and induced progressive EEG entrainment of the alpha rhythm: only the SYNC group demonstrated increased phase consistency across sessions. Furthermore, within the SYNC group, patients who exhibited stronger EEG entrainment (more consistent phase alignment session-to-session) tended to show greater clinical improvement in depression ratings. This suggests a dose–response relationship between the degree of brain rhythm modulation and antidepressant effect. However, the trial’s primary outcome found no significant difference in overall treatment response rates between the SYNC and UNSYNC groups. Both groups improved from baseline, as expected with standard rTMS, but EEG-synchronized TMS did not outperform the control condition in remission rates. The authors noted, that suboptimal timing precision in some patients and the relatively small sample might have limited the observable advantage. Nonetheless, this first RCT in the field demonstrated the feasibility of brain state-dependent TMS in a clinical setting and provided clues, that enhancing EEG entrainment could yield better outcomes. Overall, the trial reinforces the concept that EEG-synchronized rTMS can meaningfully influence brain activity in MDD, while also highlighting the need to refine synchronization.

Building upon these findings we designed the present study to rigorously test a refined EEG-synchronized rTMS intervention in MDD, guided by the converging evidence that frontal-midline theta oscillations are critically implicated in depression severity and treatment resistance. In particular, our approach focuses on the theta frequency band in the dorsomedial prefrontal cortex (DMPFC) based on accumulating evidence that elevated theta activity in medial prefrontal and anterior cingulate regions has been corelated with depression severity and resistance to conventional treatments [33–35]. Current evidence from our lab further suggests that theta activity in the left dorsomedial prefrontal cortex (DMPFC) has a higher signal-to-noise ratio than alpha activity in left DLPFC, making it a prime biomarker for targeting by EEG-triggered TMS [36]. In practical terms, the DMPFC theta rhythm may be a more robust and reliable biomarker for triggering TMS, making it an attractive target for a phase-locked stimulation paradigm. We therefore developed the BOSSFRONT2 trial to evaluate real-time EEG-triggered theta-burst stimulation of the left DMPFC as a novel therapy for treatment resistant depression. The stimulation in the experimental arm is synchronized to each patient’s endogenous frontal theta oscillation (detected via scalp EEG over DMPFC in real time), so that TMS bursts are delivered at a consistent phase of the theta rhythm. The control condition in our study is the current standard protocol: iTBS applied to the left DLPFC (the same location and protocol used in many guidelines and clinical centers). By comparing theta-synchronized DMPFC-rTMS (hereafter referred to as DMPFC-EEG-TBS) with standard open-loop iTBS (DLPFC-iTBS), our randomized double-blind trial will test whether personalized, theta oscillation-synchronized neuromodulation can achieve superior antidepressant effects. We hypothesize that engaging the pathologic theta network in a timing-specific manner will at least match, if not outperform the efficacy of conventional iTBS, while maintaining a favorable safety profile.

This pilot trial is designed as an exploratory superiority study, aiming to detect whether DMPFC-EEG-TBS yields a clinically meaningful improvement compared to standard DLPFC-iTBS. Given the pilot nature and limited sample size, the study is not powered for confirmatory testing but is intended to generate effect-size estimates necessary for planning a subsequent definitive RCT to establish the benefits of personalized, brain state-dependent TMS in MDD.

### Objectives

To study the therapeutic efficacy of four weeks (20 sessions, 5 sessions per week) of real-time EEG- synchronized rTMS of the left DMPFC compared to standard FDA-approved iTBS of the left DLPFC to reduce depressive symptoms in patients with antidepressant-resistant MDD in a controlled randomized double-blind clinical pilot trial.

### Trial design

The study is a single-site randomized controlled double-blind parallel-group clinical trial.The framework is comparative and exploratory, investigating potential superiority of the EEG-synchronized intervention over standard iTBS based on clinical outcomes.

The overall flow of participants through the trial is illustrated in Fig. 1:

**Fig. 1 Fig1:**
[figure not shown]
Flowchart of participant progress through the BOSSFRONT2 trial

## Methods: participants, interventions, outcomes

### Study setting

The study will be conducted at the Dept. of Psychiatry and Psychotherapy at the University Hospital of Tübingen. All treatments will be performed in a suitable experimental location with a qualified medical doctor available on site. The study is planned to span a total duration of 24 months.

### Eligibility criteria

Subject inclusion criteria.Subjects are between 18 to 65 years oldSubjects meet DSM-5 criteria for current major depressive disorder (MDD), confirmed with the Structured Clinical Interview for DSM-5.Subjects score 20 points or more on the Montgomery–Åsberg Depression Rating Scale (MADRS).Subjects must have had at least one non-response in accordance with the Antidepressant Treatment History Form (ATHF), meaning a failure to achieve remission in a previous pharmacological antidepressant treatment trial of sufficient dosage and duration, meaning a dose considered to be effective (e.g., superior to placebo in controlled clinical trials) and a duration needed to be sufficient to produce a robust therapeutic effect (e.g., 4–6 weeks); this treatment failure can apply for the current or any prior depressive episode. Demonstration of medication resistance for the current episode is not required, if resistance occurred during any prior depressive episode.Subjects must exhibit a sufficiently detectable frontal-midline theta rhythm during the EEG screening procedure. This is assessed with a 32-channel resting-state EEG (5 min, eyes open) conducted at the screening visit. Theta power spectra are computed and visually inspected for the presence of a clear peak in the 4–8 Hz range over midline frontal electrodes. Only patients with a discernible theta peak are eligible, as this is required to ensure feasibility of the real-time algorithm.Subject is in otherwise good physical and mental health. Subject understands the study procedures and agrees to participate in the study by giving written informed consent.Subject is willing to comply with the study restrictions (cf. “paragraph relevant concomitant care …”)If antidepressant medication is being taken, it has to be taken for at least 2 weeks before inclusion in the study and the dose or active substance must not have been changed. It is necessary that no change in medication will be made until the end of the study (last visit takes place 4 weeks after the last therapy session). If a change in medication is necessary, further study participation is not possible.

Subject exclusion criteria:Subject is under the age of legal consent.Subject has a diagnosis of bipolar disorder.Subject suffers from current symptoms of psychosis.A current major depressive episode longer than 5 years.Subject has a history of substance abuse or dependence within the past 2 years.Subject has a diagnosis of antisocial or borderline personality disorder.Subject has active suicidal ideation with plan and/or intent.Subject has a history of seizure disorder.Subject has a history of severe head injury with loss of consciousness.Subject had a prior brain surgery, or any other major psychiatric or medical comorbidity.Subjects with intake of pro-convulsive medication, e.g. imipramine, amitriptyline, doxepin, nortriptyline, maprotiline, chlorpromazine, clozapine, foscarnet, ganciclovir, ritonavir, amphetamines, cocaine, MDMA (ecstasy), phencyclidine (PCP, angel’s dust), ketamine, gamma-hydroxybutyrate (GHB), alcohol, theophylline, in accord with the present consensus guideline on safety, ethical considerations, and application of TMS in clinical practice and research [37, 38].Daily intake of benzodiazepines in equivalent doses of lorazepam > 1 mg/d.Subject has a cardiac pacemaker, implanted medication pump, intracardiac line, or acute, unstable cardiac disease.Subject has an intracranial implant (e.g., aneurysm clips, shunts, stimulators, cochlear implants, or electrodes) or any other metal object within or near the head (excluding the mouth) that cannot be safely removed.Subject has participated in another study within 2 weeks prior to the first study visit.Subject has contraindications to MRI, or does not agree that (1) the MRI is obtained for research purposes only and will not be evaluated by a radiologist; if an abnormality is present, this may well not be noticed by the doctors, scientists and other staff involved in the study and handling the MRI data; and that (2) if any of the staff involved in the study does suspect a relevant abnormality to be present in the MRI, they will reveal this to the subject so that a further diagnostic workup can be conducted outside of the study.Subject is pregnant or trying to get pregnant. If someone is not sure whether she is pregnant we will test human chorionic gonadotropin in the urine.Planned or anticipated changes of medication within the study period. If a change in medication is necessary, further study participation is not possible.

### Who will take informed consent?

Patients will be checked for eligibility by a study physician. Eligible patients will be informed about the modalities of the clinical investigation in accordance with the provided patient informed consent (IC). The patient is to be informed both in writing and verbally by the investigator before any study‐specific procedure is performed. The patient will be given sufficient time (i.e., > 24 h) to decide whether to participate in this study and to ask questions concerning this trial. The patient must give consent in writing. The patient and informing physician must each personally date and sign the informed consent form with an integrated declaration on data privacy protection.

### Additional consent provisions for collection and use of participant data and biological specimens

Not applicable.

## Interventions

### Intervention description

Subjects will be randomized to one of two arms of daily rTMS interventions for four weeks (5 sessions per week on working days, 20 sessions in total). In the experimental EEG-synchronized condition, TMS will be triggered at the trough of the theta oscillation extracted from left DMPFC. The control condition will consist of rTMS therapy applied to the left DLPFC following an FDA approved iTBS protocol [15] (s. Figure 2):Experimental arm (DMPFC-EEG-TBS):

**Fig. 2 Fig2:**
[figure not shown]
Schematic comparison of the experimental EEG-synchronized theta-burst stimulation (DMPFC-EEG-TBS) and the control condition with standard iTBS (DLPFC-iTBS)

Triple pulses at 100 Hz are delivered in bursts phase-locked to the trough of the individual theta oscillation (4–8 Hz) recorded over the left dorsomedial prefrontal cortex (DMPFC) (s. figure 2). Although rising or falling phases of theta oscillations may transiently exhibit higher instantaneous excitability, previous work has demonstrated that stimulation precisely at the trough yields the most reliable and long-lasting plasticity-like effects [30, 31, 39]. By adopting 100 Hz we rely on evidence, that higher intraburst frequencies strengthen plasticity-like effects within established safety margins [40, 41]. Extending this rationale, frequency-dependence has been shown with state-dependent bursting in motor cortex, where 100–200 Hz bursts at the trough of the ongoing μ-rhythm reliably increased cortical excitability, whereas 60 Hz did not [39]. In our protocol, bursts are phase-locked to the trough of the endogenous frontal theta oscillation over left DMPFC to exploit a receptive excitability state for plasticity induction [30]. Bursts are triggered on roughly every 15-20th trough, yielding a mean inter-burst interval of approximately 3.5 s, consistent with our prior prefrontal real-time work reporting 3.49 s (SD ± 2.01) {Gordon, 2022 #81}. A minimum inter-burst interval of 1.0 s is enforced to ensure artifactfree phase estimation following each burst. Under these constraints the session delivers 600 pulses and lasts about 11 min 38 s, as shown in Figure 2.2)Control arm (DLPFC-iTBS):

Standard intermittent theta-burst stimulation (iTBS) is applied to the left dorsolateral prefrontal cortex (DLPFC) according to FDA-approved parameters (50 Hz triplets repeated at 5 Hz, 2 s trains followed by 8 s pauses) until 600 pulses are delivered, resulting in a total duration of about 3 min 10 s.

In the experimental arm, bursts of three pulses at 100 Hz are phase-locked to the trough of the ongoing theta oscillation (4–8 Hz), ensuring synchronization with intrinsic brain rhythms. Circles highlight stimulation timing relative to the oscillatory phase. Of note, in the experimental condition, stimulation is not delivered on every detected theta trough but occurs with a mean inter-burst interval of approximately 3.5 s, corresponding to every 15th–20th theta cycle. In the control arm, bursts of three pulses at 50 Hz are delivered in a fixed 5 Hz pattern independent of the EEG signal (open-loop). Hereby each session in the control condition consists of 600 pulses applied in 2 s “on” / 8 s “off” cycles.

In both interventions, 600 TMS pulses will be delivered per session corresponding to 12.000 TMS pulses during the entire 4 weeks of TMS therapy. Stimulation intensity will be set to 120% resting motor threshold (RMT) or the highest tolerated intensity if this is below 120% RMT. If required, a ramp-up period will be used for a maximum of the first three sessions to accommodate patients that don’t immediately tolerate the desired stimulation intensity. Stereoscopic neuronavigation (Localite GmbH, Bonn, Germany) based on individual anatomical MRI data will be used to position the coil, where DMPFC and DLPFC target locations will be pre-determined based on the individual MRI data and identifying the respective target gyrus using standard anatomical methods [42].

To ensure blinding of the patients, all setup components are implemented identically in both conditions, that is, a surface EEG is recorded through a 5-channel equipment during the TMS intervention in both the experimental and in the standard condition. But only in the experimental condition is the EEG used to trigger the TMS pulses; in the control condition, the EEG is recorded but not considered for triggering the TMS pulse. To ensure double-blinding, the rater is blinded as well, as the rater must not be present during the intervention procedure and does not have access to non-rater-related documentation.

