Also, influential factors such as tolerability of the stimulation within the different treatment conditions can be relevant for clinical feasibility and the overall treatment outcome, thus such aspects will be considered with respect to the treatment arm. We expect that rTMS treatment over the DMPFC will be more comfortable than over DLPFC due to the more medial prefrontal target, yet a longer duration of the treatment needs to be endured (15–20 min). TBS over DLPFC might be more uncomfortable than TBS over DMPFC due to the more laterally located target area closer to the temporalis muscle, which might twitch under stimulation. Yet the treatment duration is shorter (3 min). Tolerability and related complaints of the patients, as well as the reasons for drop out of patients will be documented in the CRFs. Sex and gender may influence responsiveness to rTMS, although evidence is mixed. Some studies have suggested higher response rates in women [61, 62], potentially linked to hormonal influences or anatomical factors such as scalp-to-cortex distance, while others have not found significant sex-related differences in clinical outcomes [63]. Given the limited sample size of this pilot trial, we are not powered to formally test gender-specific effects. Nevertheless, we will document and report the gender distribution of participants and conduct exploratory analyses of treatment response by gender. Regarding inter-individual anatomical variability in terms of responsiveness to TMS, in the present protocol the stimulation intensity is defined relative to the resting motor threshold without correction for e.g. scalp-to-cortex distance as we prioritized adherence to the established FDA-approved iTBS standard protocol. Nevertheless, all participants undergo structural MRI, which will enable exploratory analyses of how anatomical factors may relate to treatment outcome. In a subsequent confirmatory trial, we plan to incorporate scalp-to-cortex distance correction or electric-field modeling to improve individual dose standardization.

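### Patient blinding is said to rest on identical set-up, but stimulation lasts about 3.7 times as long in the experimental arm (5.0 to 6.7 times on the Discussion's figures) with a different rhythm, so the stated measure does not secure it

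*Protocol article*

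**What the plan says.** On how patients are kept blind, the Intervention description states: "To ensure blinding of the patients, all setup components are implemented identically in both conditions". It explains this as a five-channel surface EEG recorded during stimulation in both arms and used for triggering in only one. The Therapy visit section adds that patients are not told their assignment. The Blinding section says that the therapy provider cannot be blinded and is encouraged not to disclose the allocation. The rater is kept out of the sessions and away from other documentation.

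On session length, the Intervention description says of the experimental arm: "the session delivers 600 pulses and lasts about 11 min 38 s". Of the control arm it says: "resulting in a total duration of about 3 min 10 s". The Discussion gives other figures. For the experimental arm: "yet a longer duration of the treatment needs to be endured (15–20 min"). For control: "Yet the treatment duration is shorter (3 min"). It raises the difference only as a matter of comfort and tolerability.

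The abstract, Objectives and Trial design call the trial double-blind, and the Discussion counts this among the methodological strengths.

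**The concern.** The measure offered for patient blinding equalises the equipment on the head. It does not equalise what the patient feels and hears: how long stimulation lasts and how the pulses are spaced. Those differences recur at each of 20 sessions.

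A patient with some prior knowledge could use them. The Background describes iTBS as a treatment of about 3 minutes that is increasingly standard. The section on post-trial care says that standard iTBS is routinely available in the institution's own day clinic. The exclusion criteria bar participation in another study within two weeks of the first visit, but they do not list earlier TMS treatment.

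The outcomes are open to patient belief. BDI-II and IDS-30 are self-rated. The MADRS is scored by a blinded rater but draws on what the patient reports. Under Statistical methods, rejection of the null hypothesis on MADRS is to be read as justification for a confirmatory trial, so the strength of the blinding claim affects how that result can be read.

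Separately, the experimental session has two stated lengths that cannot both describe the same 200 bursts.

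**Working it through.** **Inputs.**
- Pulses per session: "In both interventions, 600 TMS pulses will be delivered per session" (Intervention description).
- Experimental burst: "bursts of three pulses at 100 Hz are phase-locked to the trough of the ongoing theta oscillation", so three pulses per burst.
- Mean inter-burst interval: about 3.5 s, with 3.49 s cited from prior work (Intervention description; about 3.5 s again in the real-time algorithm text).
- Control pattern: triplets at 5 Hz in 2 s trains with 8 s pauses (Intervention description).
- Stated durations: 11 min 38 s = 698 s and 3 min 10 s = 190 s (Intervention description); 15–20 min = 900–1200 s and 3 min = 180 s (Discussion).

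**Step 1: reproduce the stated experimental duration.** Bursts = 600 / 3 = 200. Duration = 200 × 3.49 s = 698 s = 11 min 38 s, an exact match. With 3.5 s it is 700 s = 11 min 40 s.

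**Step 2: reproduce the stated control duration.** Triplets per train = 2 s × 5 Hz = 10, or 30 pulses. Trains = 600 / 30 = 20. Duration = 20 × 2 s + 19 × 8 s = 40 + 152 = 192 s = 3 min 12 s, in line with about 3 min 10 s.

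**Step 3: compare the arms.**

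| Source of figures | Experimental | Control | Ratio |
|---|---|---|---|
| Intervention description | 698 s | 190 s | 3.7 |
| Discussion | 900–1200 s | 180 s | 5.0–6.7 |

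Over 20 sessions this is 20 × 698 / 60 = about 233 min against 20 × 190 / 60 = about 63 min. On the Discussion figures it is 300–400 min against 60 min.

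**Step 4: compare the rhythm.** Experimental: one triplet about every 3.5 s for the whole session. Control: a triplet every 1 / 5 = 0.2 s for 2 s, then 8 s of silence, 20 times.

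**Step 5: test the second experimental duration.** For 200 bursts to take 900–1200 s, the mean interval would have to be 900 / 200 = 4.5 s to 1200 / 200 = 6.0 s, not about 3.5 s. The Discussion's figure is 900 / 698 = 1.29 to 1200 / 698 = 1.72 times the one in the Intervention description. Set-up time is not a stated explanation: the Discussion contrasts its figure with 3 min for control, which is stimulation time alone.

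**Step 6: match measures to differences.** Identical EEG set-up masks whether EEG is in use. Non-disclosure withholds the label. Neither masks duration or rhythm, and the article describes no other measure that does.

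**The case against.** The strongest reply is that this is a parallel-group trial. Each patient experiences one arm and has no second session type to compare it with. A session of 3 or of 11 minutes reveals the allocation only to someone who knows what each arm should last. Patients are not told their assignment, the consent text is not available here, and the 3-minute description of iTBS stands in the article's Introduction, not in patient material. This stands. A reader might infer from the ratios that patients will be unblinded. The document shows only that they could be.

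A reader might also infer that the trial gathers no evidence on whether blinding held. An article's silence does not support that, because the full protocol and the CRF may contain such an item.

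It is also tempting to attach a bias in favour of the novel arm. The document gives no basis for a size or a direction. Both arms receive active stimulation and the control is the approved standard, so a patient who guesses control need not expect less.

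Finally, the authors explain in the Discussion why the control was kept as the approved protocol, acknowledge that there is no sham arm, and disclose the difference in duration. That defends the choice of comparator. It does not support the claim that identical set-up ensures patient blinding, because duration is never discussed in that connection. The rater's blinding is handled separately and is not directly affected by session length.

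**Conclusion.** The point holds in limited form. The article states a property, patient blinding, and names the measure that is meant to ensure it. That measure leaves unmasked a 3.7-fold difference in stimulation time (5.0- to 6.7-fold on the Discussion's figures) and a plainly different pulse rhythm. Patient blinding is therefore not secured by what is described, and double-blind should not be listed as a strength without qualification. Whether patients in fact recognise their arm depends on what they know or are told, which the document does not show. Any effect on BDI-II, IDS-30 or, through patient report, MADRS is possible but cannot be quantified.

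The two experimental durations are a plain contradiction, and this stands whatever view is taken of blinding. The 11 min 38 s follows from the stated burst count and interval; the 15–20 min does not.

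**What to change.** 1. **Restate the blinding claim.** In the abstract, Trial design, Intervention description, Blinding section and the Discussion's list of strengths, and wherever else the label recurs, describe the trial as rater-blinded, with patients not informed of their allocation and patient blinding not assured. In the Discussion, add session length and rhythm as a limitation beside the missing sham condition. Cost: wording only.

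2. **Measure it.** If the CRF does not already hold one, add a treatment-guess item for patients, asked early (for example after the first week, before benefit can drive the guess) and again at T20, and for the rater at T20. Report it by arm. Cost: one CRF item. It can cover only patients still to be treated, since recruitment began in January 2024 and is projected to run to December 2026. Late guesses will be confounded with response.

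3. **Reconcile the durations** given in the Intervention description and in the Discussion, together with the inter-burst interval that each implies.

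None of this changes the stimulation. Keeping control patients in the chair for longer would not justify restoring the patient-blinding claim: it hides neither the rhythm nor the moment at which stimulation stops.
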